#### Primary outcome measure

a) Behavior symptoms are measured with the Neuropsychiatric Inventory (NPI), that assesses the frequency and the severity of the symptoms as well as the caregiver distress in 12 behavioral domains (delusions, hallucinations, depression/dysphoria, anxiety, agitation/aggression, elation/euphoria, disinhibition, irritability/lability, apathy/indifference, aberrant motor activity, sleep/night time behavior, and appetite/eating). NPI is given as an interview questionnaire [17]. Each domain is rated by the caregiver in terms of both frequency (1–4) and severity (1–3), yielding a composite symptom domain score (frequency×severity). The total composite score is obtained by summing up the single item scores, which may range from 0 to 144, with higher scores indicating more behavioral problems.

#### Secondary outcomes

b) Quality of life is measured using the Quality of Life-Alzheimer’s disease Scale (QOL-AD) [18]. The QOL-AD covers 13 domains of quality of life. It has good internal consistency, validity and reliability and its use is recommended by the European consensus on outcome measures for psychosocial interventions in dementia [19]. The scale presents high psychometrics properties whatever the dementia etiologies [20].

c) Functional performances are measured with the Disability Assessment in Dementia (DAD). This scale assesses 10 basic and instrumental activities of daily living and decomposed each activity into initiation, organization and efficacy. The sensitivity and reliability have been established [21].

d) Apathy is measured using the apathy inventory [22], that assesses emotional fatigue, initiative loss and interest loss. Psychometric properties are good [23].

e) Depression is assessed using Montgomery-Asberg Depression Rating Scale (MADRS) [24]. This scale explores 10 dimensions: apparent sadness, expressed sadness, inner tension, reduced sleep, reduced appetite, concentration difficulties, lassitude, inability to feel, pessimistic thoughts, suicidal thoughts. The MADRS is one of the most reliable scale to detect depressive symptoms in dementia population independently of the stage of severity [25].

f) Caregivers’ burden is assessed using the Zarit Burden Index (ZBI) [26]. The ZBI is a subjective measure of burden that includes 22 items exploring the caregiver’s perception and feelings about care situations.

g) Caregivers’ sense of competence is assessed with the sense of competence questionnaire [27].

h) Vital status and institutionalization and their dates are assessed at each follow-up using any sources of data available (main caregivers or the general practitioner).

i) Patients’ resource utilization is measured for the month prior to the visit using the Resource Use in Dementia (RUD) [28]. The RUD questionnaire was specifically designed to estimate formal resource utilization (primary and secondary care consultation, hospitalizations, social care services funded or brokered by local authorities…) as well as informal care for dementia-related activities. Primary caregivers are asked to notify the number of days and time spent for formal and informal caregiving activities provided during the month prior to the visit.

j) Process of care in relation with dementia is assessed by asking caregivers for current use of anti-dementia drug, antidepressant drug, antipsychotic drug, consultation with a specialist (memory clinic, neurologist with private activity, psychiatrist, geriatrician) in the previous 3 months, speech therapist use, presence and type of home help support, financial subsidies support, and adult day care use.

### Economic evaluation

In order to provide useful and complete information for national decision makers, we propose also an economic evaluation in this project aiming at assessing:

- the total costs of patient care and disease management from a societal perspective spanning public services (hospitalization, primary and secondary care), social care services funded by local authorities as well as indirect cost associated with informal care. The extra sessions will be fully costed to generate a program cost and cost per participant;

- the cost-effectiveness ratio, expressed at the cost per avoided institutionalization at 12 months. This will be the first study to provide this kind of ratio.

- the net benefit for the French Healthcare system to widespread OT during 4 months more.

### Sample size

The sample size was based upon: a) the primary outcome (NPI) at 8 months; b) treatment effect sizes for outcome from the pilot study and other non-pharmacologic trials; c) ability to detect a clinical significant reduction of NPI score of 5 points: expected means (standard errors) were 16 (14) for control group and 11 (11) for intervention group; and d) a type I error rate of 0.05. An effect smaller than 5% would bring us at or near levels where the study could have statistical but not clinical significance as demonstrated by Mega et al. [29]. To attain 80% power for a two-sided comparison of the two treatment groups with an estimated attrition of 15%, a sample size of 240 is required.

### Statistical analyses

Analyses will be performed by intention to treat, in that all available data will be included. Methods of imputation such as last observation carried forward are of limited utility in dementia, because the expectation is decline for the usual treatment group, and most attrition will be due to death or assessment refusal. Therefore, for primary analysis missing data will be replaced by the “missing = failure” strategy, with sensitivity analyzes using maximum bias strategies, missing value modeling and nonresponse modeling, with a particular attention on death or institutionalization of patients. Depending on the outcome distribution, linear or non-linear mixed models will test the hypotheses, including the time of measurement (within-subject factor), the experimental condition (between-subject factor) and the interaction between these two factors.

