A growing interest in OT currently exists and some trials are ongoing [7, 8]. A review has concluded that literature provided a “proof of concept” that functional decline related to dementia may be delayed via OT interventions [9]. A 5-weeks OT’s program demonstrated clinical efficacy on daily functioning at 12 weeks in the Netherlands [10–12]. Nevertheless, the intervention’s replication in another national context failed to demonstrate any effectiveness [13]. Moreover, a recent US trial failed to demonstrate that OT added to collaborative care improves daily functioning over a 2-year period. It remains unclear whether results observed in efficacy trials with convenience and homogeneous samples are similarly obtained in routine care context. Participants who are typically volunteers for such trials differ from non-volunteers providing similar levels of care [14]. Yet, real-world studies are scarce. Recently, within an observational study based on routine care practice we showed that patients benefiting from OT experienced a stabilization in their functional performances over the 3/4 months intervention period before a worsening phase [15]. They also reported a decrease of their behavioral troubles followed by a stabilization phase. The French model of OT is a short-term intervention that enters into the intimacy of the daily functioning of patients and their caregivers, and the end of the intervention can be disruptive in a context of social and psychological frail equilibrium. Moreover, planning and implementation of relays (such as speech therapists, physiotherapists or personal care assistant) after OT are crucial to maintain therapeutic approaches according to patients’ care needs. Nevertheless, these tasks are time consuming and complex to accomplish in the devoted period. This report describes a protocol being used in an ongoing randomized trial aiming to provide evidence on long-term clinical effectiveness and economic consequences of maintaining OT over 4 extra months.

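### The primary analysis fixes a missing-equals-failure rule that is undefined for the continuous NPI total and does not match the sample size

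*Protocol article*

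**What the plan says.** All references are to the protocol article.

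- **Statistical analyses**, the rule at issue: "Therefore, for primary analysis missing data will be replaced by the “missing = failure” strategy". It follows a remark that carrying the last value forward suits dementia poorly, since patients under usual care are expected to get worse and since deaths and refused assessments should cause most of the losses. Three kinds of sensitivity analysis are named (worst-case bias, models for the missing values, models for nonresponse), and deaths and moves into an institution are to receive special care. The tests use mixed models, linear or not, with terms for time, group and their interaction.
- **Primary outcome measure**: the NPI total adds up the domain ratings, and the article describes it as a value "which may range from 0 to 144, with higher scores indicating more behavioral problems".
- **Sample size**: the target is a mean difference of 5 NPI points at month 8. The planning means are 16 for control and 11 under intervention, with spreads of 14 and 11. The test is two-sided at alpha 0.05 and aims for 80% power. Attrition enters in this way: "with an estimated attrition of 15%, a sample size of 240 is required".
- **Statistical analyses**, the analysis set: "Analyses will be performed by intention to treat, in that all available data will be included".

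The article defines no failure state, responder cut-off or replacement score for the NPI.

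**The concern.** Missing-equals-failure has a clear reading when each patient either succeeds or fails. The NPI total is a score, and the trial is powered on a difference in mean scores. To apply the rule here, somebody must choose a bad score for missing values, turn the outcome into a responder variable, or move to a rank analysis. The article does none of these, yet commits the primary analysis to the rule.

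Two things are at stake. If a clearly bad score is filled in, the imputed values add variance that the sample size did not allow for, and power falls. If the arms lose different fractions of dyads, the gap in dropout is converted into a gap in mean NPI. The primary result would then depend partly on a number that the plan does not give. The rule also gives a refused assessment the same value as a death, although the article expects both among its main causes of attrition.

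**Working it through.** **Inputs.** From Sample size: means 16 and 11; spreads 14 and 11 (labelled standard errors, but 240 is reproduced only if they are standard deviations); two-sided alpha 0.05; power 80%; attrition 15%. Allocation is 1:1, so 240 gives 120 per arm. The replacement score X and any unequal dropout rates are assumptions, because the article gives neither.

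**Step 1: the plan's own figure.**
- Pooled SD = √((14² + 11²)/2) = √158.5 = 12.59.
- n per arm = 2 × (1.96 + 0.8416)² × 158.5 / 5² = 99.5, so 100.
- Inflated: 100/0.85 = 117.6, so 118 per arm, 236 in total. A t-based version gives 101, then 119 per arm, 238 in total. Both agree with 240.
- 240 less 15% leaves 102 per arm: 5 / (12.59 × √(2/102)) = 2.84, so power is 0.81.

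The stated 80% therefore belongs to an analysis in which missing dyads drop out of the comparison.

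**Step 2: equal dropout, planned effect true.** A fraction d of each arm is set to X. For an arm with mean m and SD s:
- mean = (1 − d)m + dX
- variance = (1 − d)s² + d(1 − d)(X − m)²
- SE of the difference = √((variance in control + variance in intervention)/120)

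With d = 0.15 in both arms the difference is 0.85 × 5 = 4.25 for any X.

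Example, X = 44. Control variance = 0.85 × 196 + 0.1275 × 28² = 266.6. Intervention variance = 0.85 × 121 + 0.1275 × 33² = 241.7. SE = √(508.3/120) = 2.06; 4.25/2.06 = 2.07; power 0.54.

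| X | Pooled SD | Power |
|---|---|---|
| 16 | 11.7 | 0.81 |
| 20 | 11.9 | 0.79 |
| 30 | 13.0 | 0.71 |
| 44 (control mean + 2 SD) | 15.9 | 0.54 |
| 72 (half the scale) | 23.9 | 0.28 |
| 144 (scale maximum) | 48.0 | 0.11 |

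Simulation with skewed scores and a Welch t test agrees where run (0.81 at 16, 0.71 at 30, 0.11 at 144). Filling in the worst observed score, about 75 on average, gives 0.28.

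**Step 3: no true effect (both arms 16, SD 14).** The spurious difference is (control dropout − intervention dropout) × (X − 16). Cells show difference in points / two-sided rejection rate.

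| X | 20% vs 10% missing | 17% vs 13% missing |
|---|---|---|
| 30 | 1.4 / 12% | 0.6 / 6% |
| 44 | 2.8 / 27% | 1.1 / 8% |
| 144 | 12.8 / 56% | 5.1 / 13% |

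With equal dropout the difference is 0 and the rejection rate stays near 5% at every X.

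**Step 4: the opposite imbalance, planned effect true (10% control, 20% intervention).**
- X = 30: (0.9 × 16 + 0.1 × 30) − (0.8 × 11 + 0.2 × 30) = 17.4 − 14.8 = 2.6 points.
- X = 72: (14.4 + 7.2) − (8.8 + 14.4) = 21.6 − 23.2 = −1.6 points, so the sign reverses.

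**The case against.** Several points on the other side carry weight.

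- **The rule can be given a meaning.** It could run as a worst-rank analysis, a responder cut-off or a stated bad score, and an analysis plan that is not shown might specify one. This stands, so undefined as written is accurate and meaningless is not. It does not remove the point: the article names the rule itself for the primary analysis, beside a mean-difference sample size and mixed models.
- **The harm is conditional.** This stands. A score of 16 to 20 with equal dropout leaves power at 0.79 to 0.81, and the spurious effect needs unequal dropout, for which the article gives no figures. However, a score close to the expected control mean is hardly a failure.
- **The sensitivity analyses help.** They do, and death and institutionalisation are singled out for attention. They can reveal dependence on the rule but do not repair the primary result.

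Three stronger readings are tempting but not supported.

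- A reader might infer that the rule favours the intervention, because control dyads finish their sessions about month 4. Follow-up is gathered by blinded psychologists, not at therapy visits, and the imbalance could go either way.
- A reader might see a contradiction with the inclusion of all available data. That phrase does not exclude imputing the rest.
- A reader might see a contradiction between the expected decline and the Background's account of earlier routine-care patients: "They also reported a decrease of their behavioral troubles followed by a stabilization phase". The decline is stated without naming an outcome, and the same account describes later functional worsening. For the NPI this is a tension only.

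**Conclusion.** The point holds in a bounded form. The article commits its primary analysis to a missing-data rule that is undefined for its continuous primary outcome, and that rule is not the one its sample size assumes.

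The size depends on choices the article does not state. At 15% missing in both arms, power runs from about 0.8 if the filled-in score is near the control mean down to 0.11 at the scale maximum; it is already 0.71 at 30. If dropout differs by arm, the bias can be small (6% rejection at a score of 30 with 17% vs 13% missing) or large (56% at 144 with 20% vs 10%), and it can favour either arm. The documents do not support saying that the rule will destroy the power or will manufacture a benefit; they support saying that it could, depending on the score and the balance of dropout.

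The figures rest on the planning values read as standard deviations, a comparison of month-8 means rather than the full mixed model, and assumed scores and dropout splits. The point bears on the primary result, so it should be settled before unblinding.

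**What to change.** 1. Make the primary analysis the mixed model already planned, fitted by likelihood to all observed NPI values by randomised arm, with no single-value replacement. This restores agreement with the sample size.
2. Do not impute NPI after death; report deaths by arm.
3. This model assumes data are missing at random, and death or refusal may be informative. So make the planned missing-value and nonresponse modelling concrete: delta-adjusted (tipping-point) multiple imputation, plus a rank analysis placing death worst.
4. Keep missing-equals-failure only for a binary responder outcome with a stated cut-off.

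The cost is analysis wording only, with no new data. The small downside is that the primary result then leans on the missing-at-random assumption, which item 3 is there to test.

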### Setting and participants

The study is being conducted in the South West of France; it began in 2018 and will run until 2019. Recruitment takes place through ESA (French acronym for “Equipe Spécialisée Alzheimer”) that are specialized teams of health professionals intervening at home for dementia patients. Patients are referred to ESA under medical prescription. We selected 10 ESA that were already involved in the pilot study (described elsewhere) and showed a high recruitment capacity [15]. Moreover, patients cared by these settings have been shown to be representative of the patients care by ESA at the national level [16]. All ESA staff met University research team for research compliance and human subject data collection. Eligibility criteria were pragmatically chosen to be representative of situations encountered by therapists in their routine care practice. Patients’ inclusion criteria include having a dementia diagnosis, being referred to an ESA for the first time, a MMSE score over 15, living in the community or in residential care setting and having a non-professional caregiver. Exclusion criteria are listed as follow: institutionalized patients or patients with a short-term project of institutionalization, patients with reported behavior of care refusal, patients already included in a non-pharmacological trial, patients under legal protective measures or not able to provide their written consent for participation in the study, patients or caregivers with characteristic that could affect participation (e.g.: major physical illness; sensory impairment; disability). People with dementia meeting the inclusion criteria will be recruited over an inclusion period of 10 months, this timeframe was estimated based on ESA’s inclusion capacity.

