### Study procedures and randomization

Randomization will be performed with a 1:1 ratio, and will be stratified by territory nature (urban vs rural) and presence of gerontological coordination center in the area (yes vs no) in order to avoid imbalances on major characteristics that might influence care strategies and care effectiveness (see Fig. 1). Randomization process is centralized via a website accessible for each investigator allowing random allocation. Although patients cannot be blinded to their allocation treatment, all follow-ups assessments are gathered by assessors (psychologists) blinded to treatment allocation. Even if we cannot exclude that patients or/and caregivers inform inadvertently interviewers of the treatment they are receiving, we aim to reduce this hazard by giving explicit reminders to participants before randomization and by the use of self-measure whenever it is feasible.

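### The stated mixed model names neither inclusion NPI as a covariate nor the two stratification factors, so precision available at no cost may be lost

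*Protocol article*

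**What the plan says.** All references are to the protocol article.

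- **Statistical analyses**: depending on the outcome's distribution, "linear or non-linear mixed models will test the hypotheses, including the time of measurement (within-subject factor), the experimental condition" as between-subject factor, together with their interaction. No other term is named there or elsewhere.
- **Outcome measures, Table 1**: NPI and DAD are ticked at inclusion, M4, M8 and M12. The other outcome scales are ticked at the three follow-ups only. The text above the table lists only the follow-ups as assessment times.
- **Study procedures and randomization**: 1:1 allocation "will be stratified by territory nature (urban vs rural) and presence of gerontological coordination center in the area (yes vs no"), on the ground that these area characteristics may bear on how care is given and how well it works.
- **Setting and participants**: "We selected 10 ESA that were already involved in the pilot study". The ESA (the specialised home-care team) is not a stratification factor.
- **Sample size**: the calculation is for "the primary outcome (NPI) at 8 months", as a comparison of two group means with no covariate.

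**The concern.** The article names its model terms, and as they stand they make poor use of information the trial already holds. Earlier NPI is an obvious candidate predictor of later NPI, and it is measured on everyone before treatment. There are two natural readings of the stated model, and neither adjusts for it.

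1. **Inclusion is a level of time and arm means are free there.** The M8 interaction coefficient then equals the arm difference in change from inclusion to M8. This carries the full noise of the inclusion score into the contrast, and it is worse than ignoring baseline when the inclusion–M8 correlation is below 0.5.
2. **Time covers only M4, M8 and M12.** Inclusion NPI then plays no part in the comparison.

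The same applies, on a smaller scale, to the strata. They were thought important enough to stratify on, yet the stated model does not name them. Leaving them out of a plain M8 comparison keeps their variance in the residual, so the standard error is slightly larger than the randomisation warrants.

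At stake is the power of the primary comparison. On the first reading, the tested contrast is also not the one for which the sample size was calculated.

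**Working it through.** **Inputs from Sample size**
- Effect: "ability to detect a clinical significant reduction of NPI score of 5 points".
- Spread: "expected means (standard errors) were 16 (14) for control group and 11 (11) for intervention group". The bracketed figures are labelled standard errors but work only as SDs, as the reproduction below shows. Root-mean-square SD = √((14² + 11²)/2) = √158.5 = 12.59.
- Error rates and dropout: "a type I error rate of 0.05"; "To attain 80% power for a two-sided comparison of the two treatment groups with an estimated attrition of 15" per cent.

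**Assumptions not in the article**
- r, the inclusion–M8 correlation of NPI, shown over 0.3 to 0.7.
- Equal NPI variance at inclusion and M8, and a linear model.
- R², the share of M8 variance explained by the strata (or by ESA), shown over 1% to 10%.

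**Step 1. Reproduce the planned size.** n per arm = 2 × (1.960 + 0.842)² × 158.5 / 5² = 99.5, so 100. The total is 200, and 200/0.85 = 236 after rounding up. With the t distribution, 101 per arm gives 202/0.85 = 238. The stated 240 is reproduced, as an unadjusted two-sample comparison at M8.

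**Step 2. Power of that comparison.** Completers: 240 × 0.85 = 204, or 102 per arm. SE = 12.59 × √(2/102) = 1.763. Power = Φ(5/1.763 − 1.960) = Φ(0.876) = 81%.

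**Step 3. Variance of the M8 contrast relative to Step 2**
- Baseline ignored: 1
- Change score (inclusion a free time level): 2(1 − r)
- Baseline-adjusted: 1 − r²
- Change score over adjusted: 2/(1 + r)

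| r | 2(1 − r) | 1 − r² | Ratio | Power, change score | Power, baseline ignored | Power, baseline-adjusted |
|---|---|---|---|---|---|---|
| 0.3 | 1.40 | 0.91 | 1.54 | 67% | 81% | 84% |
| 0.5 | 1.00 | 0.75 | 1.33 | 81% | 81% | 91% |
| 0.7 | 0.60 | 0.51 | 1.18 | 96% | 81% | 98% |

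Example at r = 0.3: the change-score SE is 1.763 × √1.40 = 2.086 and power is Φ(5/2.086 − 1.960) = 67%. The adjusted SE is 1.763 × √0.91 = 1.682 and power is Φ(5/1.682 − 1.960) = 84%.

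In total sample size for 80% power with 15% attrition, change score against adjusted needs 330 against 215 at r = 0.3, 236 against 177 at r = 0.5, and 142 against 120 at r = 0.7.

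**Step 4. Strata.** For an M8 comparison, adjustment multiplies the residual variance by 1 − R². Power rises from 81.0% to 81.3%, 81.7%, 82.9% and 84.8% at R² of 1%, 2%, 5% and 10%. If strata used in randomisation are left out of the model, the true two-sided error rate is about 2 × [1 − Φ(1.96/√(1 − R²))]. That is 0.048 at R² = 2% and 0.044 at 5%, so the test is slightly conservative.

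**The case against.** The strongest reply is that the article never says the analysis is unadjusted. The terms follow the word including, in one sentence of a condensed article, and the full covariate list may sit in an analysis plan that is not shown. Nor does the article say that inclusion is a level of time. The text under Outcome measures lists only the follow-ups, and for most scales time can only mean M4 to M12. If inclusion NPI is a covariate, or arm means are constrained equal at inclusion, the loss is nil. The planned 240 also reaches 80% without any adjustment.

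Much of this stands, and it rules out several stronger readings that a reader might infer:

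- **That the model contains only three terms, or uses inclusion NPI only as a time level.** The open list and the silence on inclusion do not support either. What can be said is that no adjustment is named and that both natural readings of the named terms lose precision.
- **That the trial is underpowered.** The sample size assumes no covariate gain. Power falls below target only if the change-score form is tested and r is below about 0.5, and r is not given.
- **That omitting the strata does serious harm.** The gain is small, and the effect on the error rate is conservative. Time-constant area effects also largely cancel in a change-score contrast, so the strata loss cannot simply be added to the change-score loss.
- **That an ESA term is required.** Individuals are randomised and ESA is not a stratum, so chance imbalance between arms within teams does not bias the comparison. A figure such as 7 to 17 of 24 dyads in one arm of a team presumes equal team sizes and unrestricted allocation, and the article reports neither.

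The reply does not remove the point about the terms that are stated. The article chose to name the model, and a baseline-adjusted version is at least as precise in large samples on either reading.

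**Conclusion.** The point holds as an improvement in efficiency and clarity. The stated terms leave inclusion NPI either as a free time level or unused, and both are less precise than baseline adjustment. At r = 0.5 the difference is about 10 power points (81% against 91%). Against a change-score test it is about 17 or 18 points at r = 0.3 and 2 points at r = 0.7. Against ignoring baseline it is about 4 points at r = 0.3 and 17 at r = 0.7. The strata contribute about 0.4 to 2 points at R² of 1% to 5%; including them also makes the standard error match the randomisation.

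These sizes rest on assumed values of r and R², equal variances over time, a linear model, 102 completers per arm and the bracketed figures read as SDs. The direction does not depend on the particular r. The stated analysis is not invalid, and the planned sample size is not in error.

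**What to change.** State in the analysis plan, before outcome data are analysed by arm:

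1. The primary test is the between-arm contrast in NPI at M8.
2. It comes from a mixed model of NPI at M4, M8 and M12 with arm, visit, arm by visit, and inclusion NPI as a covariate by visit. Equivalently in aim, keep inclusion as an outcome visit but constrain arm means to be equal there.
3. Territory (urban/rural) and gerontological coordination centre (yes/no) enter as fixed effects.
4. DAD, also measured at inclusion, is handled the same way.
5. A random intercept for ESA is optional; validity does not depend on it.

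The cost is wording only. Inclusion NPI and DAD are in Table 1, the strata are recorded at randomisation, and the recruiting team is known. No visit, measurement or participant is added.
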